
### Participant timeline {13}

Participants are recruited from various social media platforms. In addition, we also contacted higher education institutes such as polytechnics and universities in Singapore to send out email recruitment advertisements. Individuals who express interest in participating will be asked to complete an Eligibility Screening Questionnaire. Eligible participants who meet the predefined inclusion and exclusion criteria are contacted through email and invited to take part in the study. Participants follow the same schedule shown in Table 3, with slight differences depending on their group assignment. The study commences with the baseline assessments, comprising Baseline Cognitive Session 1 and Pre-test Social Questionnaires. Once the baseline cognitive measures have been administered, participants are pseudo-randomised into either the Training or Control groups. Participants then proceed to complete the remaining sessions outlined in Fig. 3. During the cognitive sessions, participants complete a comprehensive battery of cognitive tasks and questionnaires. In the pre-test, we focus on measuring various traits such as language skills, numeracy skills, and non-verbal intelligence. In the post-test, we administer critical outcome measures such as cognitive flexibility, working memory, inhibition, and other secondary behavioural measures. MRI sessions during both pre-test and post-test employ the same MRI scan protocol. During the 2-week interval between pre- and post-intervention phases, participants in the Training group additionally undergo a minimum of 13 Structure Learning training sessions. A detailed list of tasks that each participant will undergo at each session of the study can be found in appendix B from the supplementary information. The study is projected to span a total of 10 weeks. A time commitment of 12 and 32 h is needed for participants in the Control and Training groups respectively.

**Table 3 Tab3:** Participant schedule

		**Study period**									
**Stage**	**Screening**	**Pre-test**					**Intervention**		**Post-test**		
		**Week**									
**Session**		**1**	**2**	**3**	**4**	**5**	**6**	**7**	**8**	**9**	**10**
Screening and Enrolment	B										
Baseline Cognitive Session 1		B									
Pre-Test Social Questionnaire		B									
Matching and Scheduling			B	B							
Pre-Test Cognitive Session 2					B	B					
Pre-MRI					B	B					
Structure Learning							T	T			
Post-MRI									B	B	
Structure Learning (Testing Stage 2)*									T		
Post-Test Social Questionnaire									B	B	
Post-Test Cognitive Session 3										B	B
Post-Test Cognitive Session 4										B	B

*B* Involve BOTH Control and Training Groups

*T* Involve Training Group ONLY

^*^ Only for Training participants who advanced to Training 2 stage

**Fig. 3 Fig3:**
[figure not shown]
General participant timeline and sessions’ flow

### Sample size {14}

The present study is designed as a scoping study to provide a good estimate of the sample size needed to detect the actual training effect in subsequent studies. Hence, sample size estimation may not be that accurate since the training programme implemented in the current study is novel and effect sizes can be hard to estimate.

Behaviourally, the sample size estimation is based on a statistical power of 0.8 with type I error rate held at an alpha level of 0.05. The estimates of statistical power are all made based on a balanced sample (equal sample size for all conditions) with a 2 × 2 mixed design with one between-subject factors (Group: Control and Training) and one within-subject factor (Time: Pre-test and Post-test). The detection of a Group × Time interaction with a small effect size of *d* = 0.25 and an assumed low population correlation of 0.3 between levels of the within-factor, Time, would need 46 participants for each level in the between-factor, Group.

Sample size estimation is done separately for the different neural measures. In healthy adults, GABA spectral peak height relative to that of water in the PFC generally showed a standard deviation of 0.24. Based on past MRS studies that measure GABA in DLPFC, the detection of a small effect size in GABA spectral peak height relative to water would need 50 participants for each group. In rs-fMRI, based on a reported correlation of *r*= 0.46 between the functional connectivity of corticostriatal networks and performance measures for Structure Learning [33], we derived a sample size of 35 participants per group to detect significant correlations. Finally, as MPM is still a relatively novel scan sequence used to quantify microstructures within the brain, prior data is hence unavailable for us to perform any power computation and sample size estimation. Instead, we sampled published MPM studies that employed similar methodological analyses [52, 53] and opted for an average sample size of 34 participants per group.

Based on sample size computation of the various measures, we opted for the highest sample size of 50 participants per group to ensure sufficient statistical power to detect significant effects in all measures. With a data attrition rate of 20%, the required sample size is set at 60 participants per group.

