### Trial design {8}

Participants are recruited in batches consisting of up to 18 individuals. To establish a baseline, each batch of recruited participants undergoes a cognitive session that assesses their verbal and non-verbal intelligence, and baseline cognitive flexibility performance. Following the baseline assessment, participants are assigned to either the (1) Training group (receiving Structure Learning training) or (2) Control group (serving as a passive control without any training) using a parallel assignment method. The allocation ratio is set at 1:1 to ensure an equal distribution of participants between the two groups. Group assignment follows procedures of a randomised controlled trial but with matching constraints of age, sex, intelligence, and baseline cognitive flexibility performance between groups. Measures of executive functions can be susceptible to practice effects which can confound the study outcomes [42]. We circumvent this issue by administering most primary and secondary measures only at the post-test to both Training and Control groups. Therefore, matching the groups in the aforementioned variables is important so that we can compare critical outcome measures of the two groups at post-test to examine the effects of the Structure Learning training programme. Consequently, the study is designed as a superiority trial with the aim of demonstrating that the performance of the Training group that engages in the Structure Learning training programme will be superior to that of the Control group for primary outcome measures administered at post-test.

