### Outcomes {12}

In the present study, multiple behavioural tasks are administered to measure various cognitive constructs. Primary behavioural constructs under investigation include Structure Learning, cognitive flexibility, inhibition, and working memory. Secondary behavioural constructs under investigation include creativity, intelligence, problem-solving, language skills, numeracy skills, social tendencies, and decision making. These measures are conducted only at pre-test assessment, i.e. baseline, only at post-test assessment, i.e. after the end of structure learning training and approximately 2 months from pre-test assessment, or at both pre-test and post-test assessments. Specifically, we administered secondary behavioural constructs measuring language skills, numeracy skills, and intelligence (with the exception of the Raven’s Advanced Progressive Matrices) only at pre-test assessments as they are traits that remain relatively stable across the adult lifespan. We administered primary and secondary behavioural constructs measuring cognitive flexibility (with the exception of the Colour Shape Task), inhibition, working memory, creativity, and problem-solving only at post-test assessments to eliminate possibility of practice effects. Finally, matching tasks, i.e. Colour Shape Task and Raven’s Advanced Progressive Matrices, secondary behavioural constructs that measure social tendencies and decision making (and hence more impervious to practice effects) and all secondary neuroimaging constructs are measured at both pre and post-test assessments. Both the Control and Training groups undergo the same measures at pre and post-test assessments. However, measures for Structure Learning are collected only for the Training group. In addition, we investigate potential neural benefits of the Structure Learning training by assessing secondary neuroimaging outcomes both structurally and functionally. Detailed information regarding the individual tasks used this study can be found in Appendix B in the supplementary information.

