#### Evaluation of efficacy of Structure Learning training

We will primarily evaluate the efficacy of Structure Learning training by examining differences in post-test measures for EF between Control and Training groups. Measures will be either standardised for easier interpretations or normalised whenever possible. Means and standard deviations of either a suitable population reported in published studies or the large-scale study that is concurrently carried out by CLIC to characterise the latent construct of CF, herein termed as WP0.1, will be used for data normalisation. Parametric tests will be used to compare group differences of primary outcome measures whenever possible. Besides focusing on individual primary outcomes, we will also examine group differences with a combination of primary outcome measures that best characterise the latent constructs of cognitive flexibility, working memory, and inhibition in the structural equation modelling outcomes of WP0.1. A multivariate mixed effects model will be used to account for the nested data structure and to investigate differences between Training and Control group on these combined EF measures.

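### The behavioural power statement (46 per group, d = 0.25) does not reproduce and assumes a Group × Time interaction that most primary outcomes cannot supply

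*Protocol article*

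**What the plan says.** Under Sample size {14}, the behavioural part says that "the sample size estimation is based on a statistical power of 0.8 with type I error rate held at an alpha level of 0.05". The design is a 2 × 2 mixed layout of Group by Time (pre-test, post-test). The target is the Group × Time interaction, with an effect called small (d = 0.25) and an assumed correlation of 0.3 between the two times. The stated result is that this "would need 46 participants for each level in the between-factor, Group".

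The section then compares this with separate figures for GABA (50 per group), rs-fMRI (35) and MPM (34, taken from published sample sizes because no power computation was possible). It concludes: "we opted for the highest sample size of 50 participants per group to ensure sufficient statistical power to detect significant effects in all measures". Enrolment is set at 60 per group to allow for attrition.

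Two other sections fix when the outcomes are measured. Trial design {8} describes "administering most primary and secondary measures only at the post-test to both Training and Control groups". Outcomes {12} lists cognitive flexibility (apart from the Colour Shape Task), inhibition and working memory among the constructs tested "only at post-test assessments to eliminate possibility of practice effects". The analysis follows from that: "We will primarily evaluate the efficacy of Structure Learning training by examining differences in post-test measures for EF between Control and Training groups".

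**The concern.** There are two separate problems. First, all inputs to the behavioural calculation are printed, so 46 per group can be checked, and it does not follow from them. Second, the calculation is for a different analysis from the one planned. A Group × Time interaction needs a pre-test value, and most primary outcomes have none.

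What is at stake is the reading of the results. The protocol describes a superiority trial on primary outcomes given at post-test. Under Who will be blinded {17a}, it names planned sample size, alongside hypotheses set in advance, as protection against bias in an unblinded analysis. It also says the study should inform the size of later studies. A reader who accepts 80% power at d = 0.25 could give a null post-test comparison more weight than it deserves, and could carry a mislabelled figure into the next design.

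**Working it through.** **Inputs.** From Sample size {14}: power 0.80, alpha 0.05, two groups, two times, correlation 0.3, d = 0.25, stated result 46 per group (92 in total), final evaluable size 50 per group. Allocation is 1:1 (Trial design {8}). Sidedness is not stated; two-sided 0.05 is assumed below.

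**Step 1: the plan's own figure.** The standard test of a within-between interaction with total sample N uses a noncentral F with λ = 2N·f²/(1 − 0.3) on 1 and N − 2 degrees of freedom.

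| f | Total N | Per group | λ | Power |
|---|---|---|---|---|
| 0.25 | 44 | 22 | 7.86 | 0.782 |
| 0.25 | 46 | 23 | 8.21 | 0.800 |
| 0.25 | 92 | 46 | 16.43 | 0.980 |
| 0.125 | 92 | 46 | 4.11 | 0.518 |
| 0.125 | 100 | 50 | 4.46 | 0.553 |

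The number 46 appears exactly once, as the total N for f = 0.25. Other variants were tried: f = d/2, one-sided testing, the between-group main effect, change scores on either SD scale, ANCOVA and a post-test t test. None gives 46 per group.

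**Step 2: what d = 0.25 could mean in the interaction.** With correlation 0.3, the SD of a change score is √(2 × 0.7) = 1.183 raw SDs. A t test on change then gives:
- Reading f = d/2 = 0.125. In this formula that equals a difference in change of 0.5 raw SD: 0.5/1.183 = 0.423, and the t test at 46 per group gives the same power, 0.518. The requirement for 80% would be 89 per group.
- Reading d as a difference in change of 0.25 raw SD: 0.25/1.183 = 0.211. Power is 0.17 at 46 per group and 0.29 at 89 per group; 353 per group are needed for 80%.

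So the answer depends on a scale that the section does not define.

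**Step 3: which outcomes allow the interaction.** Among the primary tasks given to both groups, only the Colour Shape Task is measured at pre-test and post-test. Structure Learning, also primary, is collected in the Training group only. For the remaining primary tasks the planned contrast is a two-group difference at post-test.

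**Step 4: power for that contrast.** Two-sample t test, two-sided 0.05, noncentrality d·√(n/2):
- n = 50, d = 0.25: noncentrality 1.25, power 0.236.
- n = 50, d = 0.5: noncentrality 2.50, power 0.697.
- n = 50: 80% power at d = 0.566, about 0.57.
- d = 0.25: 253 per group for 80% (252 gives 0.7998).

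**The case against.** The strongest reply is that 46 was not used. The final size came from the GABA calculation, and if f = 0.25 was intended the interaction has power 0.987 at 50 per group. That is correct, and it is why the fix leaves enrolment alone. It does not rescue the post-test comparisons, which have 70% power at 50 per group even for d = 0.5.

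A second reply is that the protocol calls itself a scoping study, close to a pilot, and warns that its estimate may be inaccurate. That warning concerns the unknown size of the training effect. It does not cover a result that does not follow from the effect assumed, or a calculation for a different contrast.

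Third, 24% applies d = 0.25 to one task at a time, whereas the efficacy section also plans a multivariate mixed model on combined executive-function measures. This stands: that model's power cannot be computed from the document, and the 24% does not describe it.

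Four stronger readings are tempting and are not supported:
- *That f was certainly mistaken for d.* The exact match makes this likely, but the document does not show how the figure was obtained.
- *That 89 per group is the right size for d = 0.25.* It is right only on the f = d/2 reading, and gives 29% power if d is a 0.25 SD difference in change.
- *That no primary outcome allows an interaction.* The Colour Shape Task does.
- *That the MPM basis is hidden.* The section openly says no power computation was possible; the fault lies in then claiming adequate power for all measures.

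**Conclusion.** The point holds. The stated 46 per group for d = 0.25 is wrong on every reading tried, with actual power at that size of 52% or 17% for the interaction, depending on the scale of d. The interaction is not available for most primary outcomes. For a single-task post-test comparison with 50 evaluable per group, power is 24% at d = 0.25 and reaches 80% only at d = 0.57. These figures assume two-sided 0.05, equal groups, a t test, no covariate adjustment, and d expressed in post-test SDs. The claim of sufficient power in all measures is therefore unsupported.

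A reader might infer that the trial must enrol more people. The documents do not support that: they do not establish d = 0.25 at post-test as the effect the trial must detect, and the behavioural figure did not set the final size. What is wrong is the power that is stated.

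**What to change.** In Sample size {14}:
1. Withdraw or correct the statement that 46 per group gives 80% power at d = 0.25. Define the effect size: whether it is f or d, and which SD it refers to. Do not simply substitute 89 per group.
2. State the behavioural power for the planned two-group post-test comparison: with 50 evaluable per group, 80% at d = 0.57 and 24% at d = 0.25. Keep an interaction calculation for the Colour Shape Task only.
3. Delete the statement that 50 per group ensures sufficient power for effects in all measures.

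The cost is a rewritten section and a less favourable stated power. Enrolment, assessments and schedule do not change.

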On a neural level, we employ a multimodality approach to examine potential neural benefits brought about by the cognitive training with both functional, i.e. resting-state functional magnetic resonance imaging (rs-fMRI) and magnetic resonance spectroscopy (MRS), and structural brain scans, i.e. multi-parameter mapping (MPM). Studies adopting training protocol based on Structure Learning have showed promising preliminary results of the potential neural benefits and demonstrated that the functional connectivity of the frontal-striatal circuits could predict decision performance [33, 34]. Building on findings from previous research, we hypothesise that we will see significant correlations of performance in the Structure Learning training programme with the frontal-cortico-striatal functional connectivity. Functional connectivity measures derived from rs-fMRI allow us to investigate functional networks within the brain but not discriminate between inhibitory and excitatory mechanisms. However, cognitive flexibility changes have been associated with neurometabolite changes in the prefrontal networks controlled by glutamatergic (excitatory) pyramidal neurons and GABAergic (inhibitory) interneurons [35–37]. Furthermore, GABAergic inhibition was found to optimise perceptual learning and decision making [38, 39]. Hence, the inclusion of MRS measurement of the neurotransmitter, γ-aminobutyric acid (GABA), will complement our findings in rs-fMRI and we hypothesise that higher GABA measured in the prefrontal cortex, an indication of better suppression of irrelevant information, will correlate with better Structure Learning performance. Previously thought to be a structurally permanent feature, recent evidence suggests that the rate and pattern of myelinisation in white matter can be modulated by learning and adaptation to novel experiences (for a review [40]). These changes, otherwise known as myelin plasticity, can play a pivotal role during learning, as well as after learning for consolidation. The present study will use MPM-R1 and R2* to probe myelinisation distribution as a measure of the speed of information processing [41] in response to environmental changes. Here, we hypothesise that MPM measures that reflect the extent of myelinisation in frontal-striatal regions, particularly within the cortex, will be associated with one’s performance during the Structure Learning training.

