#### Examining functional connectivity network changes from the Structure Learning training

Functional brain networks will be extracted through spatial group independent component analysis (GICA) in CONN [66]. Preprocessed EPI data from Training and Control groups in both sessions, i.e. Pre-test and Post-test, will be included in the GICA. We will first use principal component analysis to reduce dimensionality at both participant and group levels. Participant-specific spatial maps for each component will then be subjected to GICA3 back reconstruction to estimate spatial independent neural patterns for identification of functional brain networks [66]. We will then compute intrinsic and extrinsic connectivity to examine changes in functional connectivity, i.e. post-test minus pre-test and its relation to the Structure Learning training measures. Intrinsic connectivity is computed based on the correlation between filtered time course of each voxel with every other voxel in the participant-specific component. Extrinsic connectivity is computed based on the correlations of time series between cortical ICA components with striatal regions defined using the Melbourne Subcortex Atlas (https://www.nitrc.org/projects/msa) [67]. All correlation matrixes will be standardised with Fisher *z*-transformation and averaged to derive a mean index of functional network connectivity for each participant and session. These are then correlated with behavioural index of Structure Learning performance, such as strategy index with the Robust correlation toolbox [68].

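### The sample size section claims sufficient power in all measures, but its neural figures cover one unadjusted connectivity correlation, no MPM calculation, and a GABA effect other than the one to be tested

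*Protocol article*

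**What the plan says.** Sample size {14} gives four figures per group: 46 for a behavioural Group × Time interaction, 50 for GABA, 35 for rs-fMRI and 34 for MPM.

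- **rs-fMRI:** the input is "a reported correlation of *r*= 0.46 between the functional connectivity of corticostriatal networks" and Structure Learning performance, from which "we derived a sample size of 35 participants per group to detect significant correlations".
- **GABA:** "the detection of a small effect size in GABA spectral peak height relative to water would need 50 participants for each group".
- **MPM:** "prior data is hence unavailable for us to perform any power computation and sample size estimation". The 34 is an average of the sample sizes of published studies.

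The highest figure, 50, is adopted "to ensure sufficient statistical power to detect significant effects in all measures", and recruitment is set at 60 per group to allow for 20% attrition. Alpha and power are stated only for the behavioural calculation: "statistical power of 0.8 with type I error rate held at an alpha level of 0.05".

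Objectives {7} states the connectivity hypothesis in the plural: "we will see significant correlations of performance in the Structure Learning training programme with the frontal-cortico-striatal functional connectivity". It adds a directional hypothesis for prefrontal GABA and an association for MPM measures in frontal-striatal regions.

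The neural subsections of Statistical methods {20a} set out the analyses. Changes in intrinsic and extrinsic connectivity are computed, and "These are then correlated with behavioural index of Structure Learning performance, such as strategy index". Change in GABA+ from left and right DLPFC is correlated with a behavioural index. Difference scores from MPM maps, taken within masks of ICA components, are correlated with behavioural indexes in the plural. Outcomes {12} offers the performance index, strategy choice and strategy ICD as candidates. It also says that Structure Learning measures exist only for the Training group.

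**The concern.** A size derived for one test does not carry over to a set of tests, nor a size for one kind of effect to another kind. If the index, side, map and component can all be chosen later, two things follow. Tested without adjustment, the chance of some significant neural correlate arising by accident exceeds 0.05. Tested with adjustment, the power is lower than the single-test figure suggests.

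The claim has work to do elsewhere in the protocol. Who will be blinded {17a} says that analysts know the group assignments, and relies on hypotheses set in advance and a sufficient sample size to prevent bias. Interim analyses {21b} ends data collection once usable data reach the sample size estimate for all primary and secondary outcomes. Both lean on the figures in Sample size {14}.

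**Working it through.** **1. Reproducing the 35.** Inputs: r = 0.46 (Sample size {14}); alpha 0.05 and power 0.80, stated there for the behavioural calculation and assumed here for rs-fMRI. With the Fisher z transformation, atanh(0.46) = 0.4973, and

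n = ((z₀.₉₇₅ + z₀.₈₀) / atanh(r))² + 3 = ((1.960 + 0.842) / 0.4973)² + 3 = 34.7, so 35.

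The match is exact. One-sided 0.05 with 80% power gives 28, one-sided with 90% gives 38, and two-sided with 90% gives 46. Of these, only one two-sided test at unadjusted 0.05 with 80% power gives 35.

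**2. Counting the planned tests.** The protocol gives no number, so these counts are assumptions. With one training index and one network:

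- connectivity: intrinsic and extrinsic, 2 tests (4 with two indices);
- GABA+: left and right DLPFC, 2 tests;
- MPM: R1, R2* and MT, 3 tests. Objectives {7} names R1 and R2*, and Outcomes {12} names R1 and MT.

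That is 2 to 4 tests per hypothesis, or 2 + 2 + 3 = 7 if the three hypotheses are pooled.

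**3. False-positive chance without adjustment.** For k independent tests it is 1 − 0.95^k. For correlated tests it comes from 400,000 simulated equicorrelated normal vectors with |z| > 1.96.

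| Tests | Independent | Correlation 0.5 | Correlation 0.8 |
|---|---|---|---|
| 2 | 0.10 | 0.09 | 0.08 |
| 3 | 0.14 | 0.13 | 0.10 |
| 4 | 0.19 | 0.16 | 0.11 |
| 7 (pooled) | 0.30 | 0.23 | 0.15 |

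**4. Power with adjustment, connectivity only.** Bonferroni power is Φ(atanh(0.46) × √(n − 3) − z at 1 − 0.025/k). At n = 50 the first term is 0.4973 × √47 = 3.409. At n = 48, which is 60 less 20%, it is 0.4973 × √45 = 3.336.

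| Tests k | Critical z | Power, n = 50 | Power, n = 48 |
|---|---|---|---|
| 1 | 1.960 | 0.93 | 0.92 |
| 3 | 2.394 | 0.845 | 0.83 |
| 4 | 2.498 | 0.82 | 0.80 |
| 6 | 2.638 | 0.78 | 0.76 |

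The n here is the Training group alone, since controls have no training index. The calculation also takes 0.46 as the true correlation for a post-minus-pre change, whereas the protocol cites it for connectivity against performance.

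**5. The other two modalities.** No power can be computed for MPM, because the protocol gives no effect size and says none was available. For GABA, the 50 is tied to a small effect in peak height relative to water, per group. The planned test is a correlation between change in GABA+ and a training index, for which the protocol gives no effect size.

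**The case against.** The strongest reply is that the study is well enough sized for the hypothesis that r = 0.46 concerns. The 35 was not adopted. At 50, four Bonferroni-adjusted connectivity tests keep power of 0.82. That stands, and it means the connectivity aim has no shortfall unless more than about four tests are adjusted for (three at n = 48, where four tests give 0.799).

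A second reply is that the neural aim is secondary and, under Objectives {7}, at pilot level. Sample size {14} calls the study a scoping study and concedes that its estimate may be inaccurate. A multiplicity rule for such outcomes can properly sit in an analysis plan that is not shown. This also stands, so the lack of a stated correction is not itself the point. It does not rescue an affirmative claim of power in all measures, made in the same section that reports no power computation for MPM.

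Three stronger readings are tempting, and the protocol does not support them.

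- A reader might infer that the all-measures claim rests on the single correlation of 0.46. It rests on the highest of four figures, and the 50 is the GABA figure.
- A reader might infer that any significant correlation would satisfy the hypotheses. Objectives {7} limits connectivity and MPM to frontal-striatal regions and fixes metabolite, region and direction for GABA. The connectivity matrices are averaged to a mean index.
- A reader might cross the seven measures with two indices and treat 7 × 2 = 14 tests as the minimum. One index gives 7, and the hypotheses are stated separately, with 2, 2 and 3 tests. Nor does 0.46 have any source in the protocol for GABA or MPM, so power for a pooled family cannot be derived from it.

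**Conclusion.** The concern holds in a limited form. The statement of sufficient power in all measures is not supported by the figures beside it: one is a single-test size, one has no power basis, and one is for a different effect from the planned test. For connectivity, 50 per group is adequate for up to about four adjusted correlations and falls slightly short at six (0.78). Without adjustment, the false-positive chance is about 0.08 to 0.19 per hypothesis, and 0.15 to 0.30 over seven pooled tests.

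These sizes rest on assumed test counts, on assumed correlations of 0 to 0.8 between tests, and on Bonferroni as a conservative bound. Applying alpha 0.05 and 80% power to rs-fMRI is inferred from the exact reproduction of 35. The primary behavioural comparisons are not affected.

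**What to change.** In Sample size {14}:

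- state that 35 gives 80% power for a single correlation of 0.46 at unadjusted two-sided 0.05;
- state that 50 gives about 0.93 for one such connectivity correlation, or about 0.84 at 0.05/3;
- state that no power is claimed for MPM or for the correlation of GABA+ change with a training index;
- remove the all-measures wording.

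In the three neural subsections of Statistical methods {20a}, name before analysis one key correlation per modality against one training index. For example: mean frontal-striatal extrinsic connectivity, the left-right mean of DLPFC GABA+, and one MPM parameter in one frontal-striatal mask, each against strategy ICD. Test the three with Holm at 0.05, and label every other component, side, map and index exploratory.

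The cost is wording, fewer confirmatory neural claims and a less favourable stated power. No further participants are needed.
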